### Secondary efficacy endpoints

All analyses will be conducted with and without adjustment for age, sex, type of brain injury, and severity of the injury. Time to event analysis will be analyzed similarly as the primary endpoint. The secondary outcomes are listed below:
Comparison of GCS score changes between the intervention and control groups during ICUComparison of APACHE II and SOFA scores between the intervention and control groups during ICUComparison of incidence of delirium between the intervention and control groups during ICUComparison of changes in PTH levels between the intervention and control groups during ICUComparison of time of discharge from ICU in patients treated with high-dose and low-dose vitamin D groups (during the first 28 days of admission)Comparison of time to weaning from mechanical respiratory support in patients treated with high-dose and low-dose vitamin D groups (during the first 28 days of admission)Comparison of need for a tracheostomy between the intervention and control groups during ICU stayComparison of occurrence of infections among the intervention and control groups during ICU stay

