## Background

Vitamin D is an essential hormone for calcium homeostasis and its intestinal absorption. It also has an important role in several neuromuscular activities and metabolic responses [1]. Recent studies indicated that the active form of vitamin D (calcitriol) may have a crucial function in modulating immune responses to inflammatory conditions and infectious diseases [2, 3]. According to previous data, vitamin D deficiency has been associated with a high incidence of adverse events and mortality in critically ill patients [4]. Vitamin D can induce production of anti-inflammatory cytokines and some antimicrobial proteins such as cathelicidin by macrophages and neutrophils [3]. Antimicrobial proteins are expressed significantly in the respiratory epithelium and other organs, and they could reduce risk of infections in integumentary barrier sites [5, 6]. Notably, infectious diseases such as pneumonia and sepsis are common in traumatic patients leading to more than 20% rate of death in these patients; in addition, there is a high prevalence of vitamin D deficiency in these patients; therefore, vitamin D treatment is of high importance in traumatic brain injury (TBI) patients [7–9]. Moreover, vitamin D deficiency is also related to serious complications such as coma, slow neurological recovery, and critical illness polyneuropathy in TBI patients [10, 11]. Although there has been a direct association between vitamin D deficiency and adverse clinical outcomes in critically ill patients, the data regarding vitamin D supplementation from randomized clinical trials are limited [12]. In addition, vitamin D supplementation has not been shown whether it efficiently affects the endpoints of TBI patients or not [4, 9]. The type of vitamin D supplement, route of intervention, and speed of normalization may be associated with clinical outcomes in critically ill patients [4, 9, 12]. As compared to vitamin D injection, enteral vitamin D administration seems to be more effective and is considered safe [13, 14]. To date, studies on the effects of vitamin D on TBI patients have been inadequate and could not provide definitive conclusions [15–17]. The purpose of the present study is to determine the effect of high-dose vitamin D (cholecalciferol) supplementation versus low dose on mortality rate and inflammatory cytokine levels, in critically ill TBI patients under enteral nutrition therapy at intensive care unit (ICU).

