### Proposed analysis

To determine the normal distribution of variables, the Kolmogorov-Smirnov test will be conducted. The analysis will be performed according to the intention-to-treat (ITT) test. We perfomed an independent t-test or the Mann-Whitney test for continuous variables and the chi-square or Fisher exact test for categorical variables. Repeated measure one-way analysis of variance (ANOVA) or multivariable covariance analysis (ANCOVA) will be conducted to examine differences in severity of brain injury score (GCS), APACHE II score, SOFA score, delirium score, and all variables at study baseline between the two groups. Kaplan-Meier test was conducted and compared with the use of the log-rank test for estimates of survival time. The *P* values less than 0.05 will be considered statistically significant.

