### Primary efficacy endpoint

The primary efficacy outcome for this trial will be assessed by comparing the changes in vitamin D levels and inflammatory markers (IL-6, monocyte chemoattractant protein-1 (MCP-1), and C-reactive protein (CRP)) between two groups. The rate of mortality in TBI patients until 28 days after admission (in ICU and regular ward) will be assessed in high- and low-dose vitamin D supplement groups. The impact of high dose versus low dose of vitamin D will be analyzed, with and without adjustment for age, sex, type of brain injury, and severity of injury. If the results differ after adjusting for the variables, the results of both analyses will be reported.

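### Time to weaning and time to ICU discharge take over the Kaplan-Meier and log-rank method of the mortality analysis, with death not treated as a competing event

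*Protocol article*

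**What the plan says.** The protocol article lists two time-based secondary outcomes under Secondary efficacy endpoints. One is "Comparison of time to weaning from mechanical respiratory support in patients treated with high-dose and low-dose vitamin D groups"; the other is time to ICU discharge. Both are limited to the first 28 days of admission. For their analysis the same section says "Time to event analysis will be analyzed similarly as the primary endpoint".

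The only time-to-event component of the primary endpoint is mortality: "The rate of mortality in TBI patients until 28 days after admission (in ICU and regular ward) will be assessed". The only time-to-event method anywhere in the document is under Proposed analysis: "Kaplan-Meier test was conducted and compared with the use of the log-rank test for estimates of survival time".

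The same section states "The analysis will be performed according to the intention-to-treat (ITT) test". The Exclusion criteria, however, list death before 7 days as a reason for exclusion. No section says how a death before weaning or before ICU discharge enters the analysis of those two outcomes.

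**The concern.** Kaplan-Meier and log-rank suit all-cause mortality, because nothing competes with death. Weaning and live ICU discharge differ, because death prevents both. If deaths are censored, the estimator treats the dead as patients who could still be weaned or discharged at the same rate as those still at risk. The curve then describes a setting without death.

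This matters more than usual here. The Study objectives section hypothesises that rapid correction of vitamin D deficiency lowers mortality, so the competing event is expected to differ by arm. Nor is it likely to be rare: the Background, writing of infections in trauma patients, speaks of "leading to more than 20% rate of death in these patients". A treatment that kept more patients alive long enough to be weaned could show no gain on the weaning curve.

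**Working it through.** **Inputs.** The document gives no weaning rate, discharge rate or trial mortality rate, so there is no plan figure to reproduce. All rates below are assumptions. I take 10% to 40% deaths before the event by day 28, a range around the Background's figure of more than 20%. The true 28-day incidence of weaning (or live discharge) is set at 50%, and both hazards are constant over 28 days.

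**Formulas.** Let E be the true cumulative incidence of the event, D that of death before the event, and A = -ln(1 - D - E) the total cumulative hazard over 28 days. The event's share of it is A·E/(D + E). With deaths censored, 1-KM = 1 - exp(-A·E/(D + E)).

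**Worked case, D = 20%, E = 50%.** A = -ln(0.30) = 1.204. The event's share is 1.204 × 0.5/0.7 = 0.860. 1-KM = 1 - exp(-0.860) = 57.7%, against a true 50%.

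| Deaths | True incidence | 1-KM | Excess (points) |
|---|---|---|---|
| 10% | 50% | 53.4% | 3.4 |
| 20% | 50% | 57.7% | 7.7 |
| 30% | 50% | 63.4% | 13.4 |
| 40% | 50% | 72.2% | 22.2 |

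At 20% deaths the excess is 5.7 points for a true 40% and 10.1 points for a true 60%. With 37 patients per arm, 7.7 points is about 3 patients (0.077 × 37 = 2.8).

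**Masking between arms.** Start from D = 30%, E = 50%. Then A = -ln(0.20) = 1.609, of which 1.006 is weaning and 0.604 is death. Now halve the death hazard in one arm and leave the weaning hazard unchanged. The total is 1.006 + 0.302 = 1.308. True incidence is (1.006/1.308) × (1 - exp(-1.308)) = 56.1%, and deaths are 16.8%. 1-KM depends only on 1.006, so it is 63.4% in both arms. A true difference of 6.1 points shows as zero.

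A second set of assumed rates shows the same. At a weaning hazard of 5% per day, 1-KM is 1 - exp(-1.4) = 75.3% whatever the death hazard. True incidence is 70.7%, 66.4% and 61.4% at death hazards of 0.6%, 1.2% and 2% per day.

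**The clock, checked separately.** Take D = 20%, E = 50% over 28 days from randomisation, and suppose no event can be recorded in the days between admission and randomisation. Counting to day 28 from admission leaves 28 minus the lag. With a 7-day lag, true incidence is (0.5/0.7) × (1 - exp(-1.204 × 21/28)) = 42.5%, and 1-KM is 1 - exp(-0.860 × 21/28) = 47.5%. Lags of 2 and 4 days give true incidences of 48.1% and 46.0%. The admission clock therefore lowers the day-28 figure.

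**The case against.** The strongest reply is that the document never says deaths are censored. Kaplan-Meier and log-rank are named for survival time. The sentence carrying the primary method over follows one on adjusted and unadjusted analyses, so it may partly refer to adjustment. Deaths could be kept at risk to day 28 as never weaned or discharged, which fits the named method and removes the overstatement. This stands to the extent that censoring is the default of the method and not a written rule. It does not remove the point, because the document names a method designed for an outcome without competing events and makes no exception for two outcomes that have one.

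A second reply also stands. With deaths censored, log-rank remains a valid comparison of cause-specific hazards. In the masking example those hazards are equal, so a null log-rank result is correct for that question. It does not answer whether more patients are weaned or discharged alive.

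A reader might go further and infer that weaning or discharge could come out in the direction opposite to mortality. The calculations show a masked difference, not a reversal.

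A reader might also infer that counting from admission adds to the overstatement. It works the other way, as shown. A lag of a full week needs admission to mean the first ICU of a transferred patient. The document does not say so, and Study assessments equates baseline with ICU admission. Any lag is also balanced between arms in expectation.

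**Conclusion.** The concern holds for the competing event. Under default censoring of deaths, 1-KM overstates the 28-day probability of being weaned or discharged alive by about 3 to 13 points for 10% to 30% deaths at a true incidence of 50%. It can also hide a between-arm difference that arises through mortality. The sizes rest on assumed rates and constant hazards; the direction follows from censoring the deaths. The log-rank result would speak only to cause-specific hazards.

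The day-7 death exclusion bears on the same analyses. If applied, it removes early deaths altogether and makes both outcomes conditional on surviving the first week. That conflicts with the intention-to-treat statement, and the two sections must be reconciled.

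The start of the clock is a separate, minor point. The 28-day window is counted from admission, while entry needs a vitamin D result and allows transfers within a week. Follow-up after randomisation can therefore differ between patients. This is not a cause of the overstatement.

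These are secondary outcomes and the change is cheap, so the plan should be changed, but the main comparison does not depend on it.

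**What to change.** - For time to weaning and time to ICU discharge, report cumulative incidence with death as a competing event. Compare arms by Gray's test, or by a Fine-Gray model, which can also carry the planned adjustment for age, sex, type and severity of injury.
- Alternatively, use ventilator-free and ICU-free days to day 28, with death scored as the worst value, compared by the Mann-Whitney test already named under Proposed analysis.
- Keep Kaplan-Meier and log-rank for all-cause mortality.
- Keep patients who die before day 7 in these analyses, in line with intention to treat, and reconcile the Exclusion criteria with that.
- As a minor change, count time from randomisation.

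**Cost.** Mainly wording. Subdistribution results or composite days need a line of explanation for readers. If the horizon moves to 28 days after randomisation, late entrants need a few more days of follow-up.

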### Study assessments

At the beginning of the trial, demographic information, anthropometric parameters (weight (bed scale, Balas Company), estimating height from ulna length), mid arm circumference (measured by tape at the mid-point between the tip of the shoulder and the tip of the elbow), fat-free mass and fat mass (bioelectrical impedance analysis s10, InBody Company), vitamin D3 status (25-hydroxy vitamin D3, chemiluminescence method), IL-6 (ELISA kit), MCP-1 (ELISA kit), quantitative CRP (ELISA kit), PTH (ELISA kit), Ca, APACHE II score, SOFA score, and delirium score will be measured and repeated on days 7 and 14 after intervention in groups A and B. All drugs will be ordered daily upon physician’s request during ICU stay and will be recorded. For adjusting the effect of energy on final outcomes, based on ESPEN guideline for all patients, 25 kcal/kg actual body weight energy is considered [21]. Moreover, the total kilocalories and macronutrient delivered by enteral feeding will be calculated daily for all the participants. Blood samples (5 ml) will be collected at baseline (ICU admission) and 7 and 14 days after intervention at 10:00 am. Blood sample will be taken from veins and centrifuged at room temperature, then stored at − 20 °C. Finally, the samples will immediately be transferred with the cold box to a freezer − 80 °C for future inflammatory cytokine measurements. All routine biochemistry, hematology, and urine tests, until day 14, will be measured after sampling in Kamyab Hospital Lab, Mashhad, Iran. Serum IL-6, MCP-1, and CRP levels will be analyzed in the baseline and days 7 and 14 at the Immunology Lab of Bu Ali Research Institute, Mashhad, Iran. In addition, in case of occurrence of infections (blood stream, the urinary tract, the gastrointestinal tract, wounds, and the lung), an internist specialist will take responsibility [22]. A summary of the schedule of registration, supplementation, and study evaluation is shown in Fig. 3.

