### Non-entry criteria

Patients with hypercalcemia (Ca > 10.8 mg/dl)TBI patients who are NPO more than 48 h or have started total parenteral nutrition (TPN)Severe and active bleedingPatients treated with inotropic and corticosteroid drugsPatients treated with therapeutic dose of any vitamins and minerals apart from the routine ICU protocolPatients with body mass index (BMI) > 40 kg/m^2^ and BMI < 17 kg/m^2^History of any disease such as autoimmune disorders, cancer, sepsis, infection, liver disorder, kidney disorder, diabetes, heart failure, and metabolic diseasesKnown pregnancy and lactationPatients who are transferred from other ICUs after > 1 week

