### Study design and setting

We will include 74 TBI patients with epidural hemorrhage (EDH), subdural hemorrhage (SDH), and subarachnoid hemorrhage (SAH) as diagnosed according to computed tomography (CT) scan or magnetic resonance imaging (MRI) findings by the neurosurgeon. Patients will receive vitamin D (cholecalciferol) drop (100,000 IU) or 1000 IU identical control drop in a 1:1 ratio through random assignment method. Vitamin D drops are manufactured by Zahravi Company under good manufacturing practice (GMP). Each vial of vitamin D drop is produced to be dissolved completely in 1 ml of extra virgin olive oil (Familia Company), through a nasogastric tube (NGT) for 5 days in TBI patients. Both high-dose and low-dose drops will have the same bottle, flavor, and aroma to the blinded.

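### The marker baseline is tied to ICU admission but follow-up to the intervention, so the change score can include an untreated period; this costs precision and does not bias the group comparison

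*Protocol article*

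**What the plan says.** All references are to the protocol article.

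- **Sampling times (Study assessments):** "Blood samples (5 ml) will be collected at baseline (ICU admission) and 7 and 14 days after intervention at 10:00 am".
- **A second description of baseline (same section):** the list of measurements, which includes IL-6, MCP-1 and CRP, opens with "At the beginning of the trial, demographic information, anthropometric parameters" and says that they "will be measured and repeated on days 7 and 14 after intervention in groups A and B". The start of the trial need not be the moment of ICU admission.
- **Endpoint (Primary efficacy endpoint):** the primary outcome is assessed by "comparing the changes in vitamin D levels and inflammatory markers (IL-6, monocyte chemoattractant protein-1 (MCP-1), and C-reactive protein (CRP)) between two groups". The planned analyses are "with and without adjustment for age, sex, type of brain injury, and severity of injury".
- **Treatment (Study design and setting):** the drops are given "through a nasogastric tube (NGT) for 5 days in TBI patients".
- **Steps before the first dose:** Inclusion criteria require a 25(OH)D level below 20 ng/ml and family consent before the intervention. Non-entry criteria bar "TBI patients who are NPO more than 48 h or have started total parenteral nutrition (TPN"), so a patient kept nil by mouth for up to 48 h is not barred.

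The text sets no maximum time from admission to first dose and asks for no pre-dose sample on the dosing day.

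**The concern.** One change score is built on two time zeros. The first value belongs to ICU admission and the later values to the intervention. Whatever a marker does between admission and the first dose is then counted in the change, although no study drug has been given. A laboratory result, a family decision and a usable tube must come first, so this gap is unlikely to be zero, and its length is likely to vary between patients.

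Two things are at stake. Patient-to-patient variation in the gap adds variance unrelated to the drug to the marker endpoint, and IL-6 is the variable on which the trial is sized. In addition, the mean change within an arm cannot be read as change under treatment. The listed adjustment covariates (age, sex, type and severity of injury) include neither the gap nor the baseline marker value.

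**Working it through.** **1. The anchors side by side.**

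| Item | Time zero in the text | Section |
|---|---|---|
| Baseline blood sample | ICU admission | Study assessments |
| Baseline measurements | Start of the trial | Study assessments |
| Second and third samples | 7 and 14 days from the intervention (first or last dose not stated) | Study assessments |
| Limit on admission to first dose | None stated | – |

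**2. The plan's own figure, as a reference point.** Sample size gives 62 patients in total for alpha 0.05, 80% power and effect size 0.5. The usual two-sided formula gives 2 × (1.96 + 0.84)² / 0.5² ≈ 62.8, so 63 per arm and 126 in total. The stated total is therefore not reproduced. That is a separate matter and nothing here depends on it. I use 31 per arm (62 / 2) only as the reference size. Power there is Φ(0.5 / √(2/31) − 1.96) = Φ(0.009) = 50.3%.

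**3. Effect on the mean difference.** Let G be the gap in days, s the untreated fall per day in units of the SD of change, and τ the treatment effect. Then

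E(change, arm A) − E(change, arm B) = τ − s × [E(G in A) − E(G in B)].

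The drug cannot affect a gap that ends at the first dose, and allocation is random and blinded. The bracket is therefore zero in expectation and the contrast equals τ.

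**4. Effect on the spread.** With the SD of change set to 1 when there is no gap, and g the between-patient SD of G, the SD becomes √(1 + (s × g)²). The documents give neither s nor g. **Assumed range:** s from 0.1 to 0.5 SD per day, g from 0.5 to 2 days. The difference to detect stays at 0.5.

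| s (SD/day) | g (days) | SD factor | Total N for 80% power | Power, 31 per arm |
|---|---|---|---|---|
| no drift | – | 1.00 | 126 | 50.3% |
| 0.1 | 0.5 | 1.001 | 126 | 50.2% |
| 0.1 | 2 | 1.020 | 132 | 48.8% |
| 0.3 | 1 | 1.044 | 138 | 47.0% |
| 0.3 | 2 | 1.166 | 172 | 39.3% |
| 0.5 | 1 | 1.118 | 158 | 42.1% |
| 0.5 | 2 | 1.414 | 252 | 28.5% |

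Middle case: √(1 + 0.3²) = √1.09 = 1.044. Extreme case: √(1 + 1²) = 1.414.

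**5. Simulation with no treatment effect** (20,000 trials, 31 per arm, gamma-distributed gaps).

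| s | Mean gap (days) | SD of gap (days) | Mean within-arm change | Between-arm difference | Type I error |
|---|---|---|---|---|---|
| 0.3 | 1.4 | 1 | −0.42 SD | −0.002 | 5.0% |
| 0.5 | 2.8 | 2 | −1.41 SD | −0.002 | 5.1% |

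The within-arm change absorbs the untreated drift (0.3 × 1.41 = 0.42). The between-arm difference and the error rate are unaffected beyond simulation noise.

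**The case against.** The strongest reply is that the endpoint is a comparison between randomised, blinded arms, so untreated drift is shared on average. This stands. A reader might infer from the two anchors that the estimated treatment effect is biased; steps 3 and 5 show that it is not. A gap of equal length in every patient would add no variance at all.

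A reader might also measure the harm by the share of the admission value lost before dosing. With a 48 h gap and half-times of 1, 2 or 3 days, 1 − 2^(−2/h) gives 75%, 50% or 37%. The half-times and the gap are both assumed, and the result is neither a bias nor a loss of power. The nil-by-mouth criterion bars some patients; it does not say that first doses come 48 h late.

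Other inferences go beyond the text:

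- Counting days 7 and 14 from the end of the 5-day course would put them near days 12 and 19, and two hospitals might count differently. Nothing shows that either happened. Routine tests run to day 14, which fits a count from the start somewhat better, and Figs 2 and 3, not shown here, may settle it.
- The 10:00 am draw may apply only to the follow-up samples, so it shows no conflict with admission.
- Transfers from another ICU within a week affect time since injury. A pre-dose baseline would not remove that variation.

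Finally, the mention of ICU admission may be a loose label for enrolment, and an article leaves visit windows to the full protocol. That is possible. But the sampling sentence names admission outright for the primary markers, and the start of the trial is not tied to the first dose either. The stated rule can be improved whatever the figures show.

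**Conclusion.** The point holds as one of precision and interpretation. As written, the primary marker change can span an untreated period with no stated limit, probably of different length in different patients, and the listed covariates do not address it. The between-group comparison remains unbiased with nominal type I error, provided that blinding holds until the first dose.

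The documents do not give the size of the loss. Under the assumed range, the SD factor runs from 1.00 to 1.41. In the middle case it is 1.04, and power at 31 per arm falls from 50.3% to 47.0%. The loss is large only where fast drift and widely spread gaps coincide. The calculation assumes linear drift and a gap unrelated to the other sources of variation. That the markers drift before dosing is itself an inference. Within-group changes should not be presented as change under treatment.

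**What to change.** Define the marker baseline as the last sample before the first study dose, and keep the admission draw for the 25(OH)D screen. The cost is one sentence of protocol text and one small extra tube when admission and first dose fall on different days.

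Trial status reports recruitment complete on December 21, 2019, so for samples already drawn the remedy lies in analysis and reporting. State which sample served as baseline, report the admission-to-first-dose and injury-to-first-dose intervals by arm, and adjust the marker models for the interval and the baseline marker value. This needs no new blood but depends on the times of injury, admission, sampling and first dose having been recorded, which the article does not confirm. Adjustment removes only the part of the drift that the model captures.

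As a clarification only, state whether days 7 and 14 count from the first or the last dose, in agreement with Figs 2 and 3.
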